
### Measures

#### Demographics

Demographic information, including age, education level, race or ethnicity, socioeconomic status, gender, and sexual orientation will be obtained via self-report to accurately characterize participants.

#### BISA Interview

The BISA is a semistructured interview tool containing a series of questions regarding loss of consciousness and alterations in consciousness (eg, dizziness, memory loss, feeling stunned or disoriented, or seeing stars or spots) following potential BI due to IPV and provides a BI load summary score with a range of 0 to 8 (Table 1) composed of frequency, recency, and severity subscores [5,32]. The frequency score provides an estimate of the number of previous BIs, the recency score probes the time since the most recent event resulting in a BI and the time of the interview, and the severity score indicates whether a moderate-to-severe BI was ever sustained. The BISA tool has been useful in capturing the effects of IPV-BI on resting-state brain activation [32], white matter diffusions [13], brain morphology [33], cognitive-motor function [34], and BI symptoms [35]. Thus, the literature suggests that it will be appropriate to assess for previous BI and to assess a reliable subjective measure to allow strong inferences about BI and function.

**Table 1 table1:** Scoring Brain Injury Severity Assessment (BISA) interview. Frequency (scale range 0-4), recency (scale range 0-3), and severity (scale range 0-1) are 3 subscales of the BISA tool. The BISA tool provides a summary score ranging from 0 to 8.

Subscales and score			Description
**Frequency**			
	0	There have been no previously reported brain injuries	
	1	There have been 1 to 5 previously reported brain injuries	
	2	There have been 6 to 10 previously reported brain injuries	
	3	There have been 11 to 15 previously reported brain injuries	
	4	There have been ≥16 previously reported brain injuries	
**Recency**			
	0	The event occurred >52 weeks ago	
	1	The event occurred between 27 and 52 weeks ago	
	2	The event occurred between 14 and 26 weeks ago	
	3	The event occurred within the past 13 weeks	
**Severity**			
	0	The presence of exclusively mild brain injuries	
	1	At least 1 episode involving loss of consciousness for >30 minutes or a period of posttraumatic amnesia for >24 hours had occurred (indicating moderate-to-severe brain injury)	

#### Mental Health Screening Tools

Each participant will undergo a mental health screen that includes clinical evaluations of abuse history, anxiety, depression, PTSD, substance use, and childhood trauma. These instruments listed in Textbox 3 will be explained and administered to each participant by the research coordinator.

Mental health screening tools.
**Tools**
*Adverse Childhood Experience Questionnaire:* This is a 10-item questionnaire designed for administration to people aged ≥18 years. Questions cover family dysfunction; physical, sexual, and emotional abuse and neglect by parents or caregivers; peer violence; witnessing community violence; and exposure to collective violence [36]. It is a reliable [37] and valid [38] tool for the measurement of childhood trauma and negative health outcomes in adulthood. This was effectively used in exploring whether individuals exposed to physical and sexual abuse in childhood or domestic violence–prone environments are more likely to be involved in intimate partner violence (IPV) later in their life [39].*Conflict Tactics Scale-2 (CTS-2):* The CTS-2 (an updated version of the CTS tool) is a self-report 39-item survey measuring both the extent to which partners in a dating, cohabiting, or marital relationship engage in psychological and physical attacks on each other and their use of reasoning or negotiation to deal with conflicts [40]. Scoring for the CTS-2 involves assigning numerical values to responses and calculating subscale sores. Each question on the CTS-2 asks the participant to report the frequency of a specific behavior in the past year, with responses including 0=this has never happened, 1=once in the past year, 2=twice in the past year, 3=three to 5 times in the past year, 4=six to 10 times in the past year, 5=eleven to 20 times in the past year, 6=>20 times in the past year, and 7=not in the past year but it did happen before. To calculate a subscale score, the scores for each item in that subscale are added together. The CTS-2 has been shown to be valid and demonstrates reliable stability across its subscales: psychological aggression (*r*=0.69), physical assault (*r*=0.76), injury (*r*=0.70), and negotiation (*r*=0.60). However, the reliability coefficient for sexual coercion is noticeably weaker (*r*=0.30) [41].*Posttraumatic stress disorder (PTSD) checklist for Diagnostic and Statistical Manual of Mental Disorders (DSM)-5 (PCL-5):* The PCL-5 is a 20-item self-report measure that assesses the presence and severity of PTSD symptoms [42]. Items on the PCL-5 correspond with DSM-5 criteria for PTSD. The PCL-5 can be used to quantify and monitor symptoms over time, to screen individuals for PTSD, and to assist in making a provisional or temporary diagnosis of PTSD. The PCL-5 is composed of 20 items, each from 0 (not at all) to 4 (extremely). The total score for PCL-5 is calculated by adding together the scores for each of the 20 items. Each item is scored between 0 and 4, so the total score will range from 0 to 80. A cut-off score of 33 is often used, suggesting a high likelihood of PTSD [43]. The PCL-5 exhibits robust reliability, with impressive internal consistency (Cronbach α=0.94) and notable test-retest reliability (*r*=0.82) [42] and validity [44]. Furthermore, there was a strong relationship between current PTSD symptoms and meeting criteria for all 4 DSM-5 PTSD symptom clusters in women with IPV-caused brain injury [45].*Generalized Anxiety Disorder Scale (GAD-7):* The GAD-7 is a 7-item self-report inventory used for measuring the severity of anxiety [46]. The questions ask about common symptoms of anxiety the participant had during the past 2 weeks, such as worrying, being restless, being easily annoyed, and fearing. Each question is rated on a scale of 0 to 3, with higher scores indicating higher levels of anxiety. The total score ranges from 0 to 21. The GAD-7 is a quick and reliable tool for identifying the presence and severity of generalized anxiety disorder symptoms [46].*Patient Health Questionnaire-9 (PHQ-9):* The PHQ-9 is a 9-item self-report measure used to assess the levels of depression. The questions ask about common symptoms of depression the participant had during the past 2 weeks, such as feeling hopeless, having little energy, and difficulty concentrating [47]. Response options range from 0 (not at all) to 3 (nearly every day). The total score for the PHQ-9 ranges from 0 to 27, with higher scores indicating greater severity of depressive symptoms [48]. The validity and reliability of the PHQ-9 have been established in various studies [48]. The PHQ-9 questionnaire has been used to evaluate depression symptoms in individuals who have experienced IPV [49].*Alcohol Use Disorders Identification Test (AUDIT):* The AUDIT is a 10-item screening tool developed by the World Health Organization [50] to assess alcohol consumption, drinking behaviors, and alcohol-related problems. Each item in this tool is evaluated on a 0 to 4 scale, and the total score can range from 0 to 40 [51]. It is a valid and reliable tool for measuring alcohol-related problems [52].*Somatic Symptom Severity Scale (PHQ-15):* The PHQ-15 is a 15-item questionnaire that assesses somatic symptoms of pain across different body systems [53,54]. The tool uses a rating scale ranging from 0 (not at all) to 2 (nearly every day), and total scores range from 0 to 30, with higher scores indicating more severe somatic symptoms [54,55]. The PHQ-15 is a reliable tool with a test-retest reliability of *r*=0.60 [56]. It has also been used to show that survivors of IPV have greater levels of somatic symptoms [57].*International Trauma Questionnaire (ITQ):* The ITQ is an 18-item questionnaire that assesses PTSD and complex PTSD [58]. The reliability of the ITQ has been well established, as evidenced by several publications [59,60]. Furthermore, it has been used in studies to assess the relationship between complex PTSD and the severity of IPV psychological perpetration [61,62].*Brief Irritability Test (BITe):* The BITe is a 5-item questionnaire assessing common feelings of irritability [63]. The BITe consists of questions regarding how the individual has felt in the past couple of weeks, and they rate their experience on a scale from 1 (not at all) to 6 (always). The score ranges from 5 to 30, with higher scores indicating higher levels of irritability.*Level 2-Substance Use-Adult:* This questionnaire is a 10-item screening tool developed by the US National Institute on Drug Abuse to assess substance use [64]. The participant rates each item on a 5-point scale, from 0=never to 4=nearly every day. Scores on the individual items are interpreted independently because each item inquires about the use of a distinct substance. The rating of multiple items at scores >0 indicates greater severity and complexity of substance use.

#### Outcome Measures

The following outcome measures, which will be administered by a trained member of the research team, will be used to assess resiliency, QoL, and neurocognitive function:

*Resiliency:* Resiliency will be characterized using the Connor-Davidson Resilience Scale [65]. This 25-item questionnaire measures responses to 5 factors associated with resilience on a 5-point Likert scale ranging from 0 (not true at all) to 4 (true nearly all the time). The scale has been shown to have good psychometric properties, with high internal consistency and test-retest reliability [65].*QoL:* QoL will be measured using a modified version of the Medical Outcomes Study short form-36 [66]. This 36-item questionnaire consists of 8-scaled scores covering several aspects of QoL and general health. Each scale is scored separately and transformed onto a scale that ranges from 0 to 100 for ease of comparison, with lower scores indicating a lower QoL.*Neurocognition:* Neurocognitive function will be assessed using the Creyos (formerly known as Cambridge Brain Sciences) tool [67], which consists of 12 different tasks that assess aspects of cognition, including reasoning, memory, attention, and verbal ability. The tasks include digit span, double trouble, feature match, grammatical reasoning, monkey ladder, odd one out, paired associates, polygons, rotations, spatial planning, spatial span, and token search. The tasks have been validated in studies of patients, in brain imaging studies of healthy volunteers, and in several large-scale public studies [67-69]. The Creyos tool maintains a global normative database of >75,000 participants that allows for detailed comparisons of individuals to specific populations. The tests have been shown to be valid and reliable, and a meaningful change can be calculated using the normative database [67]. Notably, all tasks, which users report to be fun and engaging, will be administered through web application or in person using a desktop or laptop and require no expert technical support to administer. Task results will be stored securely in the cloud and can be easily downloaded for offline analyses [65,69].

In addition to the tasks included in the Creyos tool, a task-switching paradigm will be used to probe executive functions [70]. A simplified version of the task that is run on an Android tablet will be used to capture executive dysfunction in this study. This simplified version has been implemented in a study (unpublished) examining head impacts and concussions in ice hockey players.

Furthermore, we will have access to the following measures collected throughout the intervention, which are incorporated within the BEARS program [23]:

*Traumatic BI-QoL (TBI-QoL) measurement system:* The TBI-QoL measurement system is a recently developed QoL measure specifically designed for people who have experienced TBI. It consists of a 20-item questionnaire covering the domains of physical health, emotional health, cognitive health, and social participation [71]. The findings of this tool would be helpful in corroborating the findings of the study short form-36.*Brainex cognitive assessment:* This is a series of tests of neurocognitive function, including assessments of symbolic thinking. The findings of this tool will be helpful in strengthening the findings of the Creyos assessment.*Functional performance indicators:* The functional performance indicators are independently derived by ABI Wellness and act as additional composite scores that are purely indicative and aim to reflect the ability of the individual to function in everyday life. The scores are created from various TBI-QoL subdomains, which were chosen to best reflect these functional performance measures.*ABI Wellness overall engagement:* The overall engagement assessment is done to provide an overview of the weekly and cumulative engagement across the different activities of the ABI Wellness 4-pillar program. The engagement is measured against the personal goal of each activity set by the facilitator.

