### Objectives

The *primary objectives* of this study protocol are as follows:

To measure the efficacy of the CSN rehabilitative intervention in terms of its impact on resiliency, QoL, and neurocognitive functionsTo evaluate the feasibility of the CSN rehabilitative intervention in terms of study recruitment, adherence, and retention

The *secondary objectives* of this study protocol are as follows:

To characterize neurocognitive function in women who have experienced IPV-BITo characterize mental health consequences in women who have experienced IPV-BI

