**Pillars**
Aerobic exerciseThe BEARS aerobic exercise pillar aims to take advantage of the neuroplastic benefit of aerobic exercise to complement and accelerate the changes occurring as a result of cognitive training [25,29]. The aerobic exercise can include, but not be limited to, running, jogging, walking, rope jumping, swimming, stationary or recumbent bicycling, Zumba or dancing, using a treadmill or rowing machine, or elliptical exercises. The key factor for aerobic exercise is the release of neurochemicals that promote neuroplasticity and cognitive recovery. For this to be accomplished, it is critical that a specific exercise intensity is reached and maintained. The modality of the exercise is not important as long as the intensity level is met and maintained for a sufficient amount of time. A participant should be working at approximately 70% to 80% of their maximum heart rate for 30 minutes, or a minimum intensity of 12 on the Borg scale must be reached and maintained for a minimum of 30 minutes. At times, when participants are not able to exercise at this intensity or for the complete duration, the facilitator will work with the participants on improving their fitness level, aiming to enhance their intensity as high as possible. The aerobic exercise pillar will be monitored and recorded using an app embedded in the BEARS program. Facilitators will ensure that clients have been allowed to participate in physical activity by their physician or that the aerobic exercise is completed under the supervision of a certified professional (eg, physiotherapists and occupational therapists). ABI Wellness acknowledges that not all clients will be able to participate in the physical activity pillar; however, all possible accommodations will be made to allow for participation.Cognitive rehabilitationThe cognitive rehabilitation pillar is focused on recovering and rebuilding higher-order cognitive functions, such as working memory, attention, and executive functions [23]. The cognitive training program used as part of the BEARS program is the Brainex program, which is a multiexercise program that specifically targets multiple brain regions and functions. The cognitive exercise being implemented is the Brainex symbol relations task, which is a computer-based cognitive exercise consisting of a sustained visual-spatial processing or relational reasoning task of progressively increasing difficulty. It requires participants to use relational reasoning on an analog clock to conceptually and automatically process relationships that increase in complexity. The participant enters the value, and feedback is presented. Once a criterion of 90% accuracy is attained over a series of consecutive responses, the complexity of the task increases. This cognitive exercise is not language dependent, so it is accessible to participants with different language backgrounds. Individually tailored goals will be set or adjusted for improving accuracy, increasing the number of correct responses per day, improving the number of sets completed per day, and lowering the time per set while maintaining accuracy. The best approach for optimal recovery adopted in this program is to focus on capacity-building rehabilitation and help individuals regain as much cognitive function as possible before using compensatory strategies to supplement and support continuing areas of impairment. Furthermore, the symbol relations assessment is incorporated within the program to measure the cognitive capacity of participants. A pilot intervention showed cognitive improvement in participants who had sustained a BI [26].Mindfulness meditationRegular mindfulness meditation has been shown to have a myriad of benefits to both the body and the mind. In particular, following BI, mindfulness can help with increasing self-awareness, and breathing techniques are very beneficial for helping to lower stress when feeling overwhelmed or frustrated [27]. Mindfulness meditation requires the client to participate in a guided meditation block that focuses on educating the client on various types of meditation and to develop their own familiarity and skill with meditation to begin practicing on their own. The critical factors for the mindfulness meditation exercise are regulation of attention, self-awareness, and engagement. The mindfulness meditation activity is monitored and tracked using the embedded app.Integrated healthThe BEARS program was developed to improve the quality of life (QoL) of individuals recovering from BI. The integrated health pillar is focused on bringing the behavioral, social, and emotional aspects of recovery and function together to complete the holistic and integrated recovery of the client. The integrated health pillar is composed of the (1) Traumatic BI (TBI)-QoL measurement system; (2) specific, measurable, attainable/achievable, realistic, and time-based (SMART) goal setting; and (3) transition planning. Using the TBI-QoL measurement system, the facilitator and the support team will be able to identify areas of concern that should be monitored or addressed during the program. The TBI-QoL measurement system is fully embedded into the BEARS program and is included as part of the intake process as well as the subsequent progress assessments. Data will be collected on each client throughout their time in the program. This allows for a deep level of understanding of the client’s initial level of function and the progress made throughout the program. A key factor of this program is effortful processing, meaning the more effort a client puts into the activities, the greater the improvement to be expected. In addition, QoL will be measured regularly to track progress in the domains of physical, emotional, cognitive, and social health. The TBI-QoL measurement system is accessible through the facilitator tracking system and the client portal. SMART goal setting allows the facilitator to help the client take small, manageable steps toward their various goals during their time in the program and teach them how to set goals for success. By working with the client with SMART goal setting, the facilitator will be providing the client with the necessary skills required to succeed upon completion of the program. In addition, transition planning is a critical component of all successful rehabilitation programs as this prepares the client for reintegration into the community and their future success.

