### Sample Size Estimation

To generate and design a study with adequate power, we estimated the required sample size based on previous data from our laboratory in both healthy participants and those with IPV-BI [34,35]. Power calculations are based on the desired end point to detect a change in each of the assessments across testing times. Therefore, assuming our published SDs for these measures and considering the potential for increased variability in this study population, a total sample size of 100 participants would provide a >90% probability that the study will detect a significant change score at a 2-sided 5% significance level.

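### Repeat cognitive testing is judged against zero change with no control, so any retest gain enters the efficacy estimate, and the training platform's own test is not independent support for it

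*Protocol article*

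**What the plan says.** - **Objective.** The first primary objective in Objectives is "To measure the efficacy of the CSN rehabilitative intervention in terms of its impact on resiliency", and it goes on to name QoL and neurocognitive function.
- **Design and timing.** Design describes a pre-post study, with a usual-care comparison left to a later study. Under Procedure (Overview), neurocognition is tested in sessions two, three and four. Session one is mental health screening, and no practice run on the cognitive tests is described.
- **Test.** Statistical Analysis compares the mean or median of each assessment across testing times by 1-way ANOVA, at P<.05.
- **A possible safeguard.** Outcome Measures says of Creyos that "a meaningful change can be calculated using the normative database". Statistical Analysis does not take this up.
- **Training.** Textbox 1 states: "The cognitive exercise being implemented is the Brainex symbol relations task". It adds that "the symbol relations assessment is incorporated within the program to measure the cognitive capacity of participants".
- **Corroboration.** Outcome Measures lists a Brainex cognitive assessment, a series of tests that includes symbolic thinking, and says: "The findings of this tool will be helpful in strengthening the findings of the Creyos assessment".
- **Limitations.** The absence of a control group is acknowledged. Practice or retest gain is not mentioned anywhere in the article.

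**The concern.** There are two linked problems.

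First, people often score better on a cognitive test simply because they have taken it before. With no control group and a null of zero change, the planned comparison cannot separate that gain from an effect of the program. The estimate is their sum.

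Second, the supporting evidence comes from the platform that delivers the training. Improvement on a test close to the practised task is expected whether or not anything carries over to untrained tasks, and carry-over is what Creyos is there to show. If both measures rise, a reader of the results would see two agreeing tests where there may be only practice on one and training progress on the other.

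At stake is the meaning of a positive cognitive result, which the Abstract's Conclusions already anticipate.

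**Working it through.** **1. The plan's own figure.** Sample Size Estimation gives "a total sample size of 100 participants" and power above 90% to "detect a significant change score at a 2-sided 5% significance level", and says "Power calculations are based on the desired end point to detect a change in each of the assessments across testing times". No effect size, SD or correlation is stated, so the figure cannot be reproduced. Solved backwards for a paired change (dz = mean change / SD of change):

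dz = (1.960 + 1.282)/√100 = 0.324 (0.327 with the t distribution).

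**2. Inputs for the check.** From the documents: N = 100, two-sided 5%, one arm, null of zero change. Assumed, because the documents give neither: retest gain g = 0.1 to 0.3 baseline SD, and correlation between occasions r = 0.5 to 0.8. The true treatment effect is set to zero and all 100 are taken to complete.

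**3. Formula.** dz = g/√(2(1−r)). The chance of a significant improvement is the upper tail of the noncentral t with 99 df and noncentrality dz × √100. For g = 0.2 and r = 0.7: dz = 0.2/√0.6 = 0.258, noncentrality 2.58, chance 72.5%.

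| r | g = 0.1 | g = 0.2 | g = 0.3 |
|---|---|---|---|
| 0.5 | 16.6% | 50.8% | 84.4% |
| 0.6 | 19.7% | 60.0% | 91.3% |
| 0.7 | 24.8% | 72.5% | 97.0% |
| 0.8 | 34.7% | 87.9% | 99.7% |

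At r = 0.8 a 0.2 SD retest gain has dz = 0.2/√0.4 = 0.316, almost the 0.324 that the study is sized to detect.

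**4. Sensitivity to the test and to dropout.**
- Three-occasion within-subject ANOVA, 0.2 SD gain at both retests (simulated, 3,000 runs per setting): 64%, 77% and 92% for r = 0.6, 0.7 and 0.8.
- The same data analysed as independent groups: 13%, 9% and 4.5%. With a 0.3 SD gain this rises to 52% to 55%.
- Dropout, g = 0.2 and r = 0.5: 51% at n = 100, 42% at 80 and 33% at 60.

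**5. Effect of a corrected null.** With g = 0.2, r = 0.7 and no treatment effect (20,000 simulated trials), testing against zero is significant in 72.7%. Testing against the known retest gain is significant in 5.1%, the nominal level within simulation error.

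**6. Brainex, by reading.** Textbox 1 makes a Brainex task the exercise that is trained and builds an assessment of that skill into the program. Table 2's example day has two 40-minute cognitive blocks. At two days a week this is 2 × 2 × 40 = 160 minutes a week, or about 160 × 12 / 60 = 32 hours over 12 weeks. Outcome Measures then offers a Brainex series that includes symbolic thinking as support for Creyos. After that exposure, a gain on overlapping tests is expected without any transfer.

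**The case against.** The strongest reply is that retest gain is one consequence of having no control group, which Limitations openly concedes and which a later comparative study is meant to address. Practice-corrected scoring of Creyos is also the kind of detail that an unseen analysis plan could hold. Both points have force: the single-arm design is not itself the finding, and an analysis plan may adjust for practice. Neither reaches the sentence that offers Brainex as support, nor the use of efficacy as the label for an uncontrolled change. Both stand in the article.

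Several stronger readings are tempting and are not supported:

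- A reader might infer that Brainex simply retests the trained task. The article speaks of symbolic thinking within a series of tests and never equates it with the symbol relations assessment. Overlap is probable, and other tests in the series may be untrained.
- A reader might take 90% accuracy as the endpoint of training. Textbox 1 uses it as the criterion for raising difficulty.
- A reader might conclude that an inert program would certainly be declared effective, or that at least one of the 12 Creyos tasks would almost certainly be positive. The first depends on assumed gains and correlations. The second also needs the tasks to be independent, which the documents do not say. Moreover, Brainex is a supporting measure with no decision rule attached.
- A reader might suppose that the Creyos norms supply the correction. The article does not say that they contain retest data.

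**Conclusion.** The point holds in a limited form. As stated, the analysis counts any retest gain on Creyos and task switching in the efficacy estimate, and the Brainex assessment cannot serve as independent evidence of transfer. That follows from the text without any assumed number.

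The size is illustrative only. About 51% to 88% per score for a 0.2 SD gain rests on a paired or repeated-measures test, 100 completers, no treatment effect and r = 0.5 to 0.8. The full assumed range runs from about 17% to 99.7%. An independent-groups ANOVA would give much lower figures, but it would be the wrong model for repeated measurements on the same women.

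This should be corrected because it changes what a positive cognitive result can be taken to mean. It does not require a change of design.

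**What to change.** 1. In Outcome Measures, delete the sentence that has Brainex strengthening the Creyos result, and report Brainex as a training-progress measure.
2. In the first primary objective and the conclusions, describe the cognitive results as uncontrolled within-person change that includes practice. Add practice to Limitations.
3. If the Creyos normative source holds retest data at a comparable interval, add an analysis of change against the expected retest gain, with the proportion of participants beyond the reliable-change limit. If it does not, show the results over a range of assumed retest gains. Do the same for task switching, for which the article describes no norms.

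No new arm, visit or data collection is needed. Items 1 and 2 are wording only. Item 3 costs some analysis and depends on what the normative source contains. The downside is that the cognitive effect will look smaller, and norms from a general population may not fit these participants or the 3-month program and follow-up intervals. Six participants were enrolled as of October 2023, so at that date the change could still precede any outcome analysis.
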